1  
General  
information

**Protocol reference Id**

20\_000270

**Study title**

Association of physical conditions with challenging behaviours in people with intellectual disabilities: a longitudinal cohort study of a national sample of primary-care patients in England using the Clinical Practice Research Datalink

**Research Area**

Disease Epidemiology

**Does this protocol describe an observational study using purely CPRD data?**

Yes

**Does this protocol involve requesting any additional information from GPs, or contact with patients?**

No

**Sponsor**

University of Glasgow

**Funding source for the study**

Is the funding source for the study the same as Chief Investigator's affiliation?

Yes

**Funding source for the study**

University of Glasgow

**Institution conducting the research**

Is the institution conducting the research the same as Chief Investigator's affiliation?

Yes

**Institution conducting the research**

University of Glasgow

**Method to access the data**

Indicate the method that will be used to access the data

Institutional multi-study licence

Is the institution the same as Chief Investigator's affiliation?

Yes

**Institution name**

University of Glasgow

**Extraction by CPRD**

Will the dataset be extracted by CPRD

No

**Multiple data delivery**

This study requires multiple data extractions over its lifespan

No

**Data processors**

|                          |                                              |
|--------------------------|----------------------------------------------|
| Data processor is | Same as the chief investigator's affiliation |
| Processing        | Yes                                          |
| Accessing         | Yes                                          |
| Storing           | Yes                                          |
| Processing area   | UK                                           |

**Primary care data**

CPRD GOLD

CPRD Aurum

**Do you require data linkages**

Yes

**Patient level data**

HES Admitted Patient Care

Mental Health Services Data Set (MHSDS)

**NCRAS data****Covid 19 linkages****Area level data****Do you require area level data?**

Yes

**Practice level (UK)**

Practice Level Index of Multiple Deprivation

**Patient level (England only)**

Patient Level Index of Multiple Deprivation

**Withheld concepts**

**Are withheld concepts required?**

No

**Linkage to a dataset not listed**

**Are you requesting a linkage to a dataset not listed?**

No

**Patient data privacy**

**Does any person named in this application already have access to any of these data in a patient identifiable form, or associated with an identifiable patient index?**

No

**Lay Summary**

Previous studies have shown that people with intellectual disabilities commonly engage in challenging behaviours such as physically, verbally or sexually aggressive, destructive or self-injurious behaviour, but prevalence rates vary significantly between studies. Association of challenging behaviours with behavioural, psychiatric and psychosocial factors has been established previously, but physical conditions such as pain, sleep problems, constipation, epilepsy, urinary/bowel incontinence and sensory impairments have been less studied and existing evidence is mostly of low quality and inconclusive. In this study, we will investigate the incidence of challenging behaviours in a large nationwide population of primary care patients with intellectual disabilities. We will also examine the association between challenging behaviours and physical conditions in this population, including exploring how different health (e.g. severity of intellectual disabilities, co-occurring autism/genetic syndromes/mental comorbidities), demographic (e.g. age, gender, ethnicity) and socioeconomic (e.g. Practice/Patient Level Index of Multiple Deprivation) factors may affect this relationship. The results of this study will help us understand whether presence of challenging behaviours in patients with intellectual disabilities is affected by their physical health and how other factors may further impact this association.

**Technical Summary**

Challenging behaviours can include physically, verbally or sexually aggressive, destructive or self-injurious behaviour. The estimated prevalence of challenging behaviour problems in intellectual disabilities in large population studies shows considerable variation between 4–22%, with multiple factors likely to underlie challenging behaviours in this population. Risk factors associated with challenging behaviours in people with intellectual disabilities include male gender, severe/profound level of intellectual disabilities, co-occurring autism and deficits in receptive and expressive communication. An association with behavioural, psychiatric and psychosocial factors has also been established, but physical conditions such as pain, sleep problems, constipation, epilepsy, urinary/bowel incontinence and sensory impairments have been less studied and existing evidence is mostly of low quality and inconclusive. In this study, we will investigate the incidence of challenging behaviours in a large nationwide population of primary care patients with intellectual disabilities in England. Using stratified Cox proportional hazard models, we will also examine the association between challenging behaviours and physical conditions (i.e. pain, sleep problems, constipation, epilepsy, urinary/bowel incontinence and sensory impairments) in this population, including exploring how different health (e.g. severity of intellectual disabilities, co-occurring autism/genetic syndromes/mental comorbidities), demographic (e.g. age, gender, ethnicity) and socioeconomic (e.g. Practice/Patient Level Index of Multiple Deprivation) factors may affect this relationship.

**Outcomes to be measured**

Primary outcome: challenging behaviours as defined through READ codes in Appendix 1

Moderator: record of co-occurring physical conditions (i.e. pain, sleep problems, constipation, epilepsy, urinary/bowel incontinence and sensory impairments) as defined through READ codes

Mediators: severity of intellectual disabilities, co-occurring autism/genetic syndromes/mental comorbidities as defined through READ codes in Appendix 1

Confounding covariates: demographic (age, gender, ethnicity) and socioeconomic (Practice/Patient Level Index of Multiple Deprivation) factors

## **Objectives, specific aims & rationale**

The aim of this project will be firstly to investigate longitudinal trends in the incidence of challenging behaviours in a nationwide population of primary care patients with intellectual disabilities, using data from the Clinical Practice Research Datalink. We will also investigate if there is an association between physical conditions and challenging behaviours in patients with intellectual disabilities and what the nature and direction of this association may be.

The project aims to answer the following research questions:

1. What is the 1-, 5- and 10-year incidence of challenging behaviours in a nationwide population of primary care patients with intellectual disabilities?
2. Do physical conditions (i.e. pain, sleep problems, constipation, epilepsy, urinary/bowel incontinence and sensory impairments) increase/decrease the incidence of challenging behaviours in primary care patients with intellectual disabilities?
3. To what extent do health factors (i.e. severity of intellectual disabilities, co-occurring autism/genetic syndromes/mental comorbidities) affect the incidence of challenging behaviours in primary care patients with intellectual disabilities?
4. Is the relationship between the presence of physical conditions and challenging behaviours in patients with intellectual disabilities accounted for by demographic (e.g. age, gender, ethnicity) and socioeconomic (e.g. Practice/Patient Level Index of Multiple Deprivation) factors?

## Study background

Challenging behaviours can include physically, verbally or sexually aggressive, destructive or self-injurious behaviour (van den Akker et al. 2020). The estimated prevalence of challenging behaviour problems in intellectual disabilities in large population studies shows considerable variation between 4–22% (Bowring et al. 2019), with multiple factors likely to underlie challenging behaviours in this population.

Results of a meta-analysis of risk factors associated with challenging behaviours in people with intellectual disabilities indicate that men with intellectual disabilities are significantly more likely to show aggression than women, and that individuals with severe/profound intellectual disabilities are significantly more likely to show self-injury and stereotypy than individuals with mild/moderate intellectual disabilities (McClintock et al. 2003). Individuals with a diagnosis of co-occurring autism are significantly more likely to show self-injury, aggression and disruption to the environment whilst individuals with deficits in receptive and expressive communication are significantly more likely to show self-injury, but overall, the meta-analysis highlighted the paucity of methodologically robust studies of risk markers for challenging behaviours in populations with intellectual disabilities (McClintock et al. 2003).

A more recent systematic review identified 38 studies investigating association of challenging behaviours with 11 behavioural, psychiatric and psychosocial factors (van den Akker et al. 2020), but association with physical conditions has been less investigated despite the fact that epidemiological studies show that patients with intellectual disabilities have more physical conditions than the general population (e.g. Cooper et al. 2015). A systematic review of studies investigating the association of physical conditions with challenging behaviours in population with intellectual disabilities identified 45 studies, which looked at general medical conditions, motor impairment, epilepsy, sensory impairment, gastrointestinal disease, sleep disorders, dementia and other conditions. Among the identified studies, there were only four high-quality and seven well-conducted observational studies. Significant and independent associations were found for challenging behaviours and urinary incontinence, pain related to cerebral palsy and chronic sleep problems, and between self-injurious behaviour and visual impairment. No association was found with hearing impairment, bowel incontinence, mobility impairment or epilepsy. Many other physical conditions were not addressed at all (de Winter et al. 2011).

Furthermore, contradicting findings on epilepsy were reported in a systematic review by Deb et al. (2020), who after sensitivity analysis, found a significantly higher rate of overall challenging behaviours in the epilepsy group compared with the non-epilepsy group in a meta-analysis of 10 studies, but the effect size was very small (0.16). Aggression and self-injurious behaviour both showed a statistically significant higher rate in the epilepsy group, with very small effect sizes (0.16 and 0.28 respectively). No significant intergroup difference was observed in the rate of stereotypy (Deb et al. 2020).

## Study type

Hypothesis testing

## Study design

Retrospective cohort study

## Feasibility counts

Records on all eligible patients with intellectual disabilities between the period of 1 January 2009 and 31 December 2019 will be analysed. The feasibility of identifying patients with intellectual disabilities in CPRD data has been successfully tested in previous research (Carey et al. 2016; 2017; Glover et al. 2019; 2020).

Carey et al. (2016) searched for any code used by the NHS Primary Care Quality and Outcomes Framework for learning disability and codes for conditions usually associated with intellectual disabilities (as is planned in the current project), such as chromosomal and metabolic disorders. This approach identified 21,859 adults (aged 18 years) registered in 451 English practices for at least 1 day between 1 January 2009 and 31 March 2013. The cross-sectional analysis reported on a subset of 408 practices that were providing high-quality data on 1 January 2012. A total of 14,751 people with intellectual disabilities aged 18–84 years who had been registered for at least 30 days on the 1 January 2012 date were included, along with 86,221 matched controls. Since our study will have a longer follow-up time (1 January 2009–31 December 2019) and will include patients with intellectual disabilities of all ages as opposed to adults only as has been done in Carey et al. (2016), we expect our sample size to be larger and, thus, have sufficient statistical power.

In the second study by Carey and colleagues (2017), 21,859 adults with intellectual disabilities, registered during 2009–13, were initially identified using an extended list of Read codes for intellectual disabilities and associated conditions. Specific analyses were based on smaller subgroups of adults with intellectual disabilities: a cross-sectional analysis of health and health-care quality on 1 January 2012 ( $n = 14,751$ ), a longitudinal analysis of mortality and hospital admissions during 2009–13 ( $n = 16,666$ ) and individual health checks ( $n = 7,510$ ). Since our study will have a longer follow-up time (1 January 2009–31 December 2019) and will include patients with intellectual disabilities of all ages as opposed to adults only as has been done in Carey et al. (2017), we expect our sample size to be larger and, thus, have sufficient statistical power.

Glover and colleagues (2019; 2020) identified people with intellectual disabilities by searching for any code used by the NHS Primary Care Quality and Outcomes Framework for learning disabilities, and codes for specific syndromes such as Down syndrome. This search identified 59,279 patients (aged 0–85+) with intellectual disabilities registered in English practices for at least 1 day between 1 April 2010 and 31 March 2014. As the proposed study will analyse data from 1 January 2009 up until 31 December 2019, the sample will likely be larger than in the cited study, and, thus, will have sufficient statistical power.

If we assume a 0.5% prevalence of intellectual disabilities in people of all ages as per findings from the Glover et al. (2019; 2020) study using a CPRD GOLD database with a follow-up period of April 2010–March 2014, then within the population of currently registered research acceptable (de-duplicated) patients ( $N=16,305,791$  in total;  $N=3,020,680$  for GOLD database and  $N=13,285,111$  for Aurum database), 81,529 patients would be expected to have intellectual disabilities on any given day. Further sample size considerations are discussed in the next section.

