### Sample size considerations

As per details provided in the 'Feasibility counts' section, if we assume a 0.5% prevalence of intellectual disabilities as per findings reported by Glover et al. (2019; 2020) using a CPRD GOLD database with a follow-up period of April 2010-March 2014, then within the population of currently registered research acceptable (de-duplicated) patients (N=16,305,791 in total; N=3,020,680 for GOLD database and N=13,285,111 for Aurum database) 81,529 patients would be expected to have intellectual disabilities on any given day. Prevalence studies of challenging behaviours in nationwide primary care samples are lacking, but if we assume that a prevalence of challenging behaviours in a population of people of all ages with intellectual disabilities in England is as described in a study of seven District Health Authorities in the UK by Emerson et al. (2001), 16.5% (N=13,452) of patients with intellectual disabilities are expected to have any form of challenging behaviours on any given day during the study follow-up period of 2009-2019, with prevalence rates for specific types of challenging behaviours expected to be much higher (e.g., 42.0% for aggressive behaviours). Given the estimated sample size, the study is expected to have sufficient statistical power. References after amendments: Emerson, E., Kiernan, C., Alborz, A., Reeves, D., Mason, H., Swarbrick, R., Mason, L., & Hatton, C. (2001). The prevalence of challenging behaviours: A total population study. *Research in Developmental Disabilities*, 22(1), 77-93.

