## Definition of the study population

Data on all patients with intellectual disabilities will be acquired from CPRD. Individuals with intellectual disabilities will be identified using Read codes in Appendix 1. Co-occurring challenging behaviours will be defined as a binary variable (present or not) based on READ codes in Appendix 1. Patients registered in a practice between January 1 January 2009 and 31st December 2019 will be included in the study. We require that their practice allows linkage to HES, MHSDS and IMD data, resulting in the inclusion of English practices. Patients who are registered at CPRD practices not participating in the linkage scheme, or who have individually opted out, will not be included.

Earliest cohort entry date will be 1/1/2009. Patients who register after 1/1/2009, or who are diagnosed with intellectual disabilities during the study period, will be followed from that date. Patients will be censored if they transfer out from their CPRD practices, or opt out before the end of the study period (31/12/2019). However, challenging behaviour diagnoses of patients who leave a CPRD practice prior to the end of the study period will be included in a sensitivity analysis.

Index case for a case would be one of the following:

- 1/1/2009 (if a patient is actively registered on this date with a diagnosis of challenging behaviours prior to 2009)
- date of diagnosis (if a patient's date of first diagnosis of challenging behaviours is after 1/1/2009 while they are registered)
- date of registration (if a patient's date of registration is after 1/1/2009 and they have a prior diagnosis to that registration)

Inclusion criteria:

- all patients with intellectual disabilities (as defined in READ codes in Appendix 1) registered at a general practice for at least six months prior to cohort entry date
- patients who receive a diagnosis of intellectual disabilities after cohort entry date and have a valid registration status for at least six months

Exclusion criteria

- patients registered at practices not participating in the linkage scheme, or who have individually opted out

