## **Exposures, outcomes and covariates**

Exposure: record of intellectual disabilities

The exposure variable will be a record of intellectual disabilities. Patients with intellectual disabilities will be identified using searches for any code included in Appendix 1, as has been done previously with CPRD (Carey et al. 2016; 2017).

Primary outcome: challenging behaviours

Outcome variables will be presence of challenging behaviours, which will be identified by Read codes in Appendix 1 (Sheehan et al. 2015; ).

Moderator: record of co-occurring physical conditions

Patients with intellectual disabilities and co-occurring physical conditions (i.e. pain, sleep problems, constipation, epilepsy, urinary/bowel incontinence and sensory impairments) will be identified using searches for any relevant READ code, as has been done previously with CPRD (e.g. Glover et al. 2017; Hosking et al. 2016).

Mediators:

severity of intellectual disabilities, co-occurring autism/genetic syndromes/mental comorbidities will be identified using searches for any code included in Appendix 1 (e.g. Glover et al. 2017; Hosking et al. 2016; Houghton et al. 2018)

Confounding covariates:

Demographic (age, gender, ethnicity) and socioeconomic (Practice/Patient Level Index of Multiple Deprivation) factors

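### Patients can enter on a genetic-syndrome code alone, so the syndrome effect in research question 3 is confounded with the route of entry to the cohort

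*Protocol*

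**What the plan says.** The protocol's 'Feasibility counts' section describes how an earlier study searched the database and adopts that search for this one. Beside learning-disability codes it used "codes for conditions usually associated with intellectual disabilities (as is planned in the current project), such as chromosomal and metabolic disorders". The parenthesis makes this a statement about the present study.

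'Exposures, outcomes and covariates' sets the entry rule: "Patients with intellectual disabilities will be identified using searches for any code included in Appendix 1, as has been done previously with CPRD". The inclusion criteria in 'Definition of the study population' rely on the same appendix. Neither section asks for a separate intellectual-disability code when a patient enters through an associated condition.

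Genetic syndromes then appear as a study variable from the same appendix: "severity of intellectual disabilities, co-occurring autism/genetic syndromes/mental comorbidities will be identified using searches for any code included in Appendix 1". Research question 3 asks "To what extent do health factors (i.e. severity of intellectual disabilities, co-occurring autism/genetic syndromes/mental comorbidities) affect the incidence of challenging behaviours", and Phase 2 of 'Data/statistical analysis' adds these factors to the Cox model at step (ii).

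**The concern.** One class of code does two jobs: it admits patients, and it defines a factor under study. A patient admitted on a genetic-syndrome code alone must fall in the syndrome group. A patient in the comparison group cannot have entered that way. By saying that these conditions are only usually accompanied by intellectual disability, the protocol allows that some patients admitted through them do not have it.

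The syndrome hazard ratio may therefore partly measure whether intellectual disability is present, when it is meant to measure what a syndrome adds among people who have it. A real association could be diluted or lost.

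The stated analyses do not remove this:

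- Adjustment covers age, sex, ethnicity and deprivation, none of which records whether intellectual disability is present.
- Severity joins the model at step (ii), but a patient with only a syndrome code probably has no severity code. The complete-case rule is stated for demographic analyses.
- The sensitivity analyses named concern patients who leave a practice and multiple imputation.
- 'Limitations of study design' discusses under-recording, but not people without intellectual disability entering the cohort.

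**Working it through.** **The plan's own figures.** 'Sample size considerations' gives "N=16,305,791 in total; N=3,020,680 for GOLD database and N=13,285,111 for Aurum database", with an assumed prevalence of 0.5%. 16,305,791 × 0.005 = 81,528.96, which rounds to the stated 81,529. 81,529 × 0.165 = 13,452.3, which matches the stated 13,452. Both reproduce, but neither says how many patients would enter on a syndrome or metabolic code alone.

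**Inputs for the bias.** None of these is in the documents, so all values are assumptions.

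- f: share of the syndrome group without intellectual disability
- r: their rate of challenging behaviours relative to syndrome patients with intellectual disability
- u: share of the comparison group without intellectual disability, with the same relative rate r
- s: syndrome group as a share of the cohort

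**Syndrome effect, clean comparison group (u = 0).** Observed ratio = true ratio × [1 − f(1 − r)]. This is exact for rates weighted by person-time and approximate for a Cox hazard ratio.

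| r | f | Factor | Assumed true ratio | Observed ratio |
|---|---|---|---|---|
| 0.2 | 10% | 1 − 0.10 × 0.8 = 0.92 | 1.30 | 1.20 |
| 0.2 | 20% | 1 − 0.20 × 0.8 = 0.84 | 1.30 | 1.09 |
| 0.2 | 30% | 1 − 0.30 × 0.8 = 0.76 | 1.30 | 0.99 |
| 0.1 | 5% | 1 − 0.05 × 0.9 = 0.955 | 1.50 | 1.43 |
| 0.1 | 25% | 1 − 0.25 × 0.9 = 0.775 | 1.50 | 1.16 |
| 0.1 | 50% | 1 − 0.50 × 0.9 = 0.55 | 1.50 | 0.83 |
| 1 | any | 1 | any | unchanged |

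**Syndrome effect, comparison group also contaminated.** Factor = [1 − f(1 − r)] / [1 − u(1 − r)]. With f = 10% and r = 0.1:

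- u = 5%: 0.91 / 0.955 = 0.953
- u = 10%: 0.91 / 0.91 = 1.000
- u = 25%: 0.91 / 0.775 = 1.174

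The bias can cancel or change direction.

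**Question 1 incidence.** Take a true syndrome ratio of 1.0 and u = 0. Incidence in the whole cohort divided by incidence in those with intellectual disability is then 1 − s·f·(1 − r). With r = 0.1:

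- s = 5%, f = 5%: 1 − 0.05 × 0.05 × 0.9 = 0.998
- s = 10%, f = 25%: 1 − 0.10 × 0.25 × 0.9 = 0.978
- s = 20%, f = 50%: 1 − 0.20 × 0.50 × 0.9 = 0.910

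Overall incidence falls by about 0.2% to 9%. The upper end needs half of the syndrome group to lack intellectual disability and syndromes to make up a fifth of the cohort.

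**The case against.** The operative definition is Appendix 1, whose content is not shown. It may hold only conditions in which intellectual disability is nearly universal, and its overlap with the genetic-syndrome list cannot be checked. That it is not shown is no fault of the plan. This limits what can be said about size, but the protocol's stated intention and the single-code rule still make entry differ between the two groups.

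A reader might infer that people without intellectual disability sit only in the syndrome group, and that questions 1 and 3 are therefore both biased downwards. The documents do not support this, for four reasons:

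- A mistaken learning-disability code places someone without intellectual disability in the comparison group, and metabolic disorders are an entry route that need not count as genetic syndromes.
- A downward direction requires a lower recorded rate of challenging behaviours in those without intellectual disability. That is plausible but not documented.
- The direct effect reaches one of question 3's four factors. For severity, autism and mental comorbidities it is indirect.
- The question 1 effect is probably small, and Phase 1 plans incidence by genetic syndrome where cell sizes allow, so readers could see the group without a syndrome separately.

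It is also fair to say that restricting to explicit codes is not neutral. If intellectual disability is coded more readily in patients who present with challenging behaviours, the restricted estimate carries a selection effect of its own. This stands. It is the reason to report both estimates and to keep the wider cohort for question 1.

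**Conclusion.** The point holds for the genetic-syndrome factor in question 3. The entry rule differs between the groups compared, and no stated adjustment or sensitivity analysis corrects for it. Under the assumption that people without intellectual disability have one fifth of the rate and form 10% to 30% of the syndrome group, with a clean comparison group, the hazard ratio is multiplied by 0.92 to 0.76. With equal rates there is no bias, and with enough false codes in the comparison group it reverses. The documents therefore fix neither size nor direction.

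Nothing here shows a material error in the question 1 incidence or a determined bias in the other question 3 factors, and no bias is claimed for question 2, the association with physical conditions. This is an inexpensive improvement to one planned contrast, and it does not invalidate the study.

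**What to change.** 1. Add a flag for entry route to the protocol: an explicit intellectual-disability code, or a syndrome or metabolic code only. Report the number of patients in each.
2. For question 3, estimate the genetic-syndrome effect among patients with an explicit intellectual-disability code, so that both groups meet the same entry condition. Start follow-up no earlier than that code, in line with the existing rule for patients diagnosed during the study. Report this beside the whole-cohort estimate.
3. For question 1, keep the wider cohort for the main incidence and repeat it in explicit-code patients as a sensitivity analysis.
4. Add to the limitations that some patients admitted through associated conditions may not have intellectual disability.

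The cost is one flag built from the existing code list and one extra analysis each for questions 1 and 3, with no new data. The restricted analyses have a smaller sample, lose true cases known only by a syndrome code, and may be affected by selective coding of intellectual disability in patients with challenging behaviours. The report should say so.
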